### Outcomes

Extensive outcome testing will be performed over the course of the study period (Table 2). Listening conditions vary per visit and per test, but include unilateral hearing with either standard or experimental CI settings, unilateral hearing with hearing aid using standard HA settings or loudness fitting measurements with CI plus hearing aid and unaided measurements. Order of testing will be determined according to a randomization schedule. This is except for CI testing, for which measurements will always start with the processor labeled with a purple triangle, as its allocated settings are already randomized.

**Table 2 Tab2:** Schedule of enrollment, interventions and assessments

Timepoint	Description	Weeks after CI activation																			
		#	−4	−3	0	1	2	3	4	5	6	7	8	10	12	16	20	26	30	34	52

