**Fig. 2 Fig2:**
[figure not shown]
Example of a daily-randomization scheme. Green and purple labels indicate which cochlear implant (CI) processor to wear

To prevent subjects from developing a preference for one of both programs during the first crucial period of adaptation to the cochlear implant, several prerequisites have been included in the randomization procedure. First, the same processor will not be allocated for more than 2 days consecutively within the first 4 weeks of CI rehabilitation. This restriction will be broadened from 4 weeks on to a maximum of 4 days consecutively. Second, to aid blinding of the participant to the intervention and in order to prevent subjects habitually preferring one processor to the other, the assignment of the two fittings across the two processors is randomized by the fitting clinician. As a result, there is a 50% chance that the experimental program will be saved on either the green or purple processor at each fitting. Participants will be blinded in that they are unaware which CI processor contains the experimental setting at any point in time. During the fitting procedures, participants will not be given any visual or verbal cues that may lead to recognizing which processor contains which settings.

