#### Word and sentence recognition

Word recognition will be evaluated with phoneme scoring over the levels 55, 65 (test-retest) and 75 dB sound pressure level (SPL) on a Dutch monosyllabic consonant-nucleus-consonant (CNC) speech recognition test. The average of test-retest values on 65 dB SPL will be the primary outcome values [49]. In addition, the Dutch Matrix Sentence test, which has been validated for repeated measures in CI recipients [50, 51], will be used through 3 listening conditions: (1) quiet, (2) with background noise and (3) with spatially separated background noise. The tests will be administered using the Oldenburg measurement applications software package developed by Hörtech gGmbH Germany. Speech stimuli will be presented at a fixed level of 65 dB SPL from a speaker at ear level at a distance of 1 m in the front (0°). Participants are asked to reconstruct sentences by selecting perceived words from a closed set using a touch screen. Target sentences are selected from a matrix of 50 words (5 columns, 10 words) with a fixed sentence order (name, verb, numeral, adjective, object) with subjects being forced to answer all columns. Each list consists of 10 sentences. When testing in the noise condition, an adaptive procedure is applied whereby stationary-speech-shaped noise is fixed at a level of 65 dB SPL while speech level is varied according to scoring performance using a logistic function [52]. Both speech and noise are presented by the same speaker. The speech reception threshold (SRT), which is defined as the signal-to-noise ratio (SNR) corresponding to a 50% correct score, will be determined. Scores will be excluded from analysis when fewer than two reversals occur or if the SNR ratio is higher than 15 dB [53]. To determine head shadow and squelch effect, and assess benefits of contralateral hearing aid use in particpants with bimodal devices, noise will also be presented from spatially separated loudspeakers as in Devocht et al. [54] with the exception of using 10 sentence-word lists instead of 20. To address potential learning effects [51] and familiarize participants with each task, two training lists will be administered in the condition to be tested first prior to each of the three matrix tests. The mean value of test and retest will be included as an outcome measure.

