### Sample size

Complementary to the new study design for clinical trials presented in this paper, thought has also been given to a different method for a priori calculation of sample size and power. Instead of calculating the estimated number of participants needed for a given research study, one could also work the other way around. After all, many clinical trials depend on the supply of patients within a selective pool and do not have any additional recruiting possibilities. This study, which is no exception to that point, will aim to include a minimum sample of 20 participants during an inclusion period of 18–24 months. A maximum of 30 participants will be included if recruitment is prosperous.

Sample size calculation is usually based on the primary study outcome, which in this study is the difference in CNC word recognition (test-retest at 65 dB SPL) between the experimental and standard CI setting after 6 months of rehabilitation. Using the concept of effect size as interpreted by Cohen’s d [64, 65], the following formula could be used to calculate sample size for a paired *t* test:

$$ \mathrm{N}=2+\left({\left({\mathrm{Z}}_{1-\upalpha /2}+{\mathrm{Z}}_{1-\upbeta}\right)}^2/{\mathrm{d}}^2\right) $$where N = sample size, *α* = type 1 error, *β* = type 2 error, d = effect size*.*

Given the idea of a restricted sample size, it can be argued that it is more valuable to rearrange this formula as to calculate effect size.
$$ \mathrm{d}=\surd \left(2+\left({\left({\mathrm{Z}}_{1-\upalpha /2}+{\mathrm{Z}}_{1-\upbeta}\right)}^2\right)/\mathrm{N}\right) $$

As a result, different outcomes in effect size can be calculated with a sample size range of 20–30 participants, an alpha range of 0.01–0.08 and a given power of 0.08. When considering a type 1 error of 0.05 and a sample size of 20, an effect size of 0.66 or larger can be detected. If 30 study participants are recruited and the alpha level is kept similar, the resulting detectable effect size is at least 0.53.

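### Always testing the purple processor first randomizes which map is tested first, but does not ensure that this order is balanced at the 6-month CNC comparison

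*Protocol article*

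**What the plan says.** Under Outcomes, the general rule is "Order of testing will be determined according to a randomization schedule". CI testing is the stated exception: "measurements will always start with the processor labeled with a purple triangle, as its allocated settings are already randomized".

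The randomization relied on is described under Daily-randomization procedure. There "the assignment of the two fittings across the two processors is randomized by the fitting clinician", with the result that "there is a 50% chance that the experimental program will be saved on either the green or purple processor at each fitting".

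Under Sample size, the outcome used for sizing is "the difference in CNC word recognition (test-retest at 65 dB SPL) between the experimental and standard CI setting after 6 months of rehabilitation", and the article says that "the following formula could be used to calculate sample size for a paired" t test. It reports a detectable effect of 0.66 with 20 participants and 0.53 with 30.

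Under Word and sentence recognition, for the Dutch Matrix test, "two training lists will be administered in the condition to be tested first prior to each of the three matrix tests". No training list is described for CNC. Table 2 lists sentence recognition in quiet among the primary outcomes, beside word recognition and patient preference.

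**The concern.** CI testing carries the main comparison, and it is the one part of testing without its own randomized order. The reason given is that the maps are already randomized over the processors. That makes the test order random, but random is not the same as balanced. At the 6-month comparison each participant contributes one difference, obtained with one map tested first. With 20 to 30 participants, a 50% chance per person can leave clearly more people with the same map first.

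If performance drifts within a session through practice or fatigue, the drift pushes the experimental-minus-standard difference one way in people tested with the experimental map first, and the other way in the rest. A plain paired t test leaves this in the error term. Recruitment is capped at 30, so lost precision cannot easily be bought back with more participants.

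**Working it through.** **Inputs.** From Sample size: N = 20 to 30, two-sided alpha 0.05, detectable d = 0.66 (N=20) and 0.53 (N=30). From Daily-randomization procedure: probability 0.5 that purple holds the experimental map. From Outcomes: purple is tested first. *Assumptions:* the assignment is a simple, independent draw per participant. The order effect π, which the article does not give, is 0, 0.25 or 0.5 SD of the paired difference (the SD without any order effect).

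**Step 1: the plan's own figures.** Inverting the printed formula N = 2 + (Z₁₋α/₂ + Z₁₋β)²/d² gives d = √[(Z₁₋α/₂ + Z₁₋β)²/(N − 2)]. With alpha 0.05 and power 0.80 this is 0.660 at N=20 and 0.529 at N=30, matching the stated 0.66 and 0.53. The power printed as 0.08 and the placing of the 2 in the rearranged formula do not reproduce them. They look typographical and do not affect this point.

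**Step 2: balance under a simple draw.** The number of participants with the experimental map first is Binomial(N, 0.5). Tail probabilities are two-sided.

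| N | Exact balance | Imbalance at least as large as |
|---|---|---|
| 20 | 10:10, 0.176 | 12:8, 0.50; 13:7, 0.26; 14:6, 0.115 |
| 30 | 15:15, 0.144 | 18:12, 0.36; 20:10, 0.099 |

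**Step 3: what an imbalance does in one realised trial.** Write each difference as Dᵢ = δ + sᵢπ + eᵢ, where sᵢ = +1 if the experimental map is tested first and −1 otherwise. With k participants at +1, the mean difference shifts by π(2k − N)/N. Over repeated draws the shift has mean zero and SD π/√N, which is 0.224π at N=20 and 0.183π at N=30. As an illustration, 14:6 with π = 0.5 SD gives 0.5 × 8/20 = 0.20 SD, against a detectable 0.66.

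**Step 4: cost in precision.** Under the simple draw the variance of Dᵢ grows by the factor 1 + π².

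- π = 0.25: factor 1.0625, SE × 1.031, effective d = 0.66/1.031 = 0.640.
- π = 0.5: factor 1.25, SE × 1.118, effective d = 0.66/1.118 = 0.590, as if 20/1.25 = 16 participants had been studied.

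Power from 100,000 simulated trials per scenario, at d = 0.66 (N=20) and d = 0.53 (N=30):

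| N | π (SD) | Simple draw, plain paired t | Balanced, plain paired t | Simple draw, order term | Balanced, order term |
|---|---|---|---|---|---|
| 20 | 0 | 0.80 | 0.80 | 0.78 | 0.80 |
| 20 | 0.25 | 0.78 | 0.78 | 0.78 | 0.80 |
| 20 | 0.5 | 0.71 | 0.72 | 0.78 | 0.80 |
| 30 | 0 | 0.80 | 0.80 | 0.79 | 0.80 |
| 30 | 0.25 | 0.78 | 0.78 | 0.79 | 0.80 |
| 30 | 0.5 | 0.71 | 0.73 | 0.79 | 0.80 |

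Type I error of the plain paired t test under the simple draw was 0.050 in every scenario.

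**Step 5: the Matrix test, separately.** For CI testing, the condition tested first is whichever map is on purple. The two training lists therefore give map-specific warm-up to the first position only. None of the figures above, which concern CNC, uses this.

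**The case against.** A reader might infer that a fixed colour order biases the trial toward one map. It does not: the colour is fixed but the map on it is not, so the expected order effect is zero and the type I error holds. The shift in Step 3 describes one realised trial. It is already part of the SE inflation in Step 4 and must not be counted as a second harm.

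A reader might also infer that the clinician's draw is unblocked, or made without a prepared list. The article says neither. The mechanism may be in the full research protocol, which is supplementary and not shown, so the probabilities in Step 2 are conditional on a simple draw.

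The order term is a matter for the SAP, which the article says will be finalized before database lock. Its absence here is no fault. It also does most of the work: at π = 0.5 SD and N=20, balance alone raises power only from 0.71 to 0.72, whereas an order term under the simple draw already gives 0.78.

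The order effect may be small. By week 26 participants have taken the CNC test at pre-assessment and at 13 visits from activation onward, and the outcome averages test and retest. That makes a large practice effect less plausible, though it does not exclude fatigue. Redrawing at each fitting also lets order partly average out in the learning-curve analyses, though not in the single 6-month comparison.

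Finally, the Matrix training lists do address general task learning, and they cannot be used to support a power claim about CNC.

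All of this stands. It limits the point to precision and leaves the fixed rule open to improvement: an SAP can adjust for order afterwards, but it cannot restore balance once the visits have taken place.

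**Conclusion.** The purple-first rule is valid but not efficient. It randomizes which map is tested first without ensuring balance at the comparison on which the trial is sized. The consequence is lost precision if there is an order effect: power of 0.80, 0.78 and 0.71 at N=20 and d = 0.66 for assumed order effects of 0, 0.25 and 0.5 SD. With no order effect nothing is lost. These figures rest on a simple draw, a plain paired t test and order-effect sizes that the article does not supply. For Matrix sentence recognition in quiet, also listed as primary, warm-up with a particular map is tied to test position; this is a separate observation without a figure. The point deserves a change because the remedy is nearly free, not because the planned comparison is unsound.

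**What to change.** Balance which map is tested first across participants at the 6-month visit. This can be done with a map-to-colour list that puts the experimental map on purple for half of the participants at that visit. Alternatively, CI testing can have its own balanced order, independent of colour. If the full protocol already contains such a list, a sentence saying so is enough.

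In the SAP, include test order in the primary paired analysis: regress the within-person difference on order coded +1/−1 and test the intercept. The same term suits the Matrix outcomes.

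The cost is one allocation list and one degree of freedom. With no order effect, balanced order plus the term still gives power of about 0.80. No extra visits, tests or participants are needed.

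For visits already completed, the order term alone can still be applied, with power of 0.78 to 0.79 in the scenarios examined.

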**Enrollment**																					
Clinical pre-assessment	CI screening selection	X																			
Informed consent		X																			
Surgery			X																		
CBCT scan				X																	
**Interventions**																					
CI experimental phase					X	X	X	X	X	X	X	X	X	X	X	X	X	X			
HA experimental phase																			X		
Clinical fitting phase																				X	X
**Assessments**																					
**Primary outcomes**																					
Patient preference	10-point VAS				X	X	X	X	X	X	X	X	X	X	X	X	X	X		X	X
Word recognition	CNC	X			X	X	X	X	X	X	X	X	X	X	X	X	X	X	X	X	X
Sentence recognition in quiet	Dutch Matrix Sentence Test				X	X	X	X	X	X	X	X	X	X	X	X	X	X	X	X	X
**Secondary outcomes**																					
Sentence recognition in noise	Dutch Matrix Sentence Test				X	X	X	X	X	X	X	X	X	X	X	X	X	X	X	X	X
Spatial hearing	SSPIN													X				X	X	X	
Listening effort									X						X			X	X	X	X
Loudness scaling	ACALOS								X						X			X	X	X	
Frequency selectivity	SMRT								X						X			X		X	
Questionnaires	SSQ-12, HUI-3, ICECAP-A			X														X		X	X
	Sound quality							X							X			X		X	X

*CBCT* cone-beam computed tomography, *CI* cochlear implant, *HA* hearing aid, *VAS* visual analogue scale, *CNC* consonant-nucleus-consonant, *SSPIN* spatial speech perception in noise, *ACALOS* Adaptive Categorical Loudness Scaling, *SSQ-12* Speech, Spatial and Qualities of Hearing, *HUI-3* Health Utilities Index-3, *ICECAP-A* Icepop Capability Measure for Older People

#### Word and sentence recognition

Word recognition will be evaluated with phoneme scoring over the levels 55, 65 (test-retest) and 75 dB sound pressure level (SPL) on a Dutch monosyllabic consonant-nucleus-consonant (CNC) speech recognition test. The average of test-retest values on 65 dB SPL will be the primary outcome values [49]. In addition, the Dutch Matrix Sentence test, which has been validated for repeated measures in CI recipients [50, 51], will be used through 3 listening conditions: (1) quiet, (2) with background noise and (3) with spatially separated background noise. The tests will be administered using the Oldenburg measurement applications software package developed by Hörtech gGmbH Germany. Speech stimuli will be presented at a fixed level of 65 dB SPL from a speaker at ear level at a distance of 1 m in the front (0°). Participants are asked to reconstruct sentences by selecting perceived words from a closed set using a touch screen. Target sentences are selected from a matrix of 50 words (5 columns, 10 words) with a fixed sentence order (name, verb, numeral, adjective, object) with subjects being forced to answer all columns. Each list consists of 10 sentences. When testing in the noise condition, an adaptive procedure is applied whereby stationary-speech-shaped noise is fixed at a level of 65 dB SPL while speech level is varied according to scoring performance using a logistic function [52]. Both speech and noise are presented by the same speaker. The speech reception threshold (SRT), which is defined as the signal-to-noise ratio (SNR) corresponding to a 50% correct score, will be determined. Scores will be excluded from analysis when fewer than two reversals occur or if the SNR ratio is higher than 15 dB [53]. To determine head shadow and squelch effect, and assess benefits of contralateral hearing aid use in particpants with bimodal devices, noise will also be presented from spatially separated loudspeakers as in Devocht et al. [54] with the exception of using 10 sentence-word lists instead of 20. To address potential learning effects [51] and familiarize participants with each task, two training lists will be administered in the condition to be tested first prior to each of the three matrix tests. The mean value of test and retest will be included as an outcome measure.

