### Current hypotheses

Here, it is hypothesized that hearing outcomes with a CI will improve when electrical stimulation is matched as closely as possible to the natural tonotopy of a normal hearing human brain, instead of relying on plasticity to adapt to an induced mismatch. The imaging-based, individual fitting strategy is thought to give rise to a steeper learning curve, and result in better performance in challenging listening situations, improve sound quality, and better complement residual acoustic hearing in the contralateral ear. The experimental hearing aid fit is expected to restore natural loudness perception as much as possible and to be preferred by research subjects. The suitability of the novel trial design will be considered concurrently with the investigation of these hypotheses.

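### Dropping speech-in-noise scores above 15 dB SNR makes exclusion depend on the outcome: it discards informative pairs, costs power and usually, though not always, shrinks the map difference on this secondary outcome

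*Protocol article*

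**What the plan says.** The rule stands in the protocol article under Word and sentence recognition: "Scores will be excluded from analysis when fewer than two reversals occur or if the SNR ratio is higher than 15 dB". The same paragraph fixes the direction of the scale, since the SRT is the value "which is defined as the signal-to-noise ratio (SNR) corresponding to a 50% correct score"; a larger value means the listener needs a more favourable signal. It also says: "The mean value of test and retest will be included as an outcome measure".

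The article does not say whether the limit applies to each run or to the test-retest mean, or what happens to the other map's score at the same visit. It gives a removed score no replacement value or rank.

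Table 2 lists "Sentence recognition in noise" among the secondary outcomes and schedules it from activation onwards. It bears on the hypothesis under Current hypotheses that the experimental map will "result in better performance in challenging listening situations". The sample size rests on another outcome: "the difference in CNC word recognition (test-retest at 65 dB SPL) between the experimental and standard CI setting after 6 months of rehabilitation".

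**The concern.** Each participant is their own control, so the information lies in the within-person difference. A participant who scores 10 dB on one map and fails the 15 dB limit on the other shows clearly which map served them worse. The rule removes that pair because of its result. This also fits poorly with the plan, under Statistical methods, to analyse everyone in the intention-to-treat population.

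At stake is the in-noise comparison. With 20 to 30 participants, each lost pair costs precision. If the experimental map is the worse one for some people, the rule can mask that as readily as it can mask a benefit.

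**Working it through.** **The plan's own figure.** The article gives no figure for speech in noise. Its detectable effect sizes belong to the CNC word score. They follow from its formula N = 2 + (Z₁₋α/₂ + Z₁₋β)²/d², solved for d with two-sided alpha 0.05 and power 0.80 (printed as 0.08):

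- N = 20: √[(1.960 + 0.842)²/18] = √(7.85/18) = 0.66
- N = 30: √(7.85/28) = 0.53

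Both match the stated values. They say nothing about the in-noise outcome, so the rest rests on assumed SRT distributions.

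**How often each map is hit.** For one score per map, P(SRT > 15) = 1 − Φ[(15 − μ)/√(σ_b² + σ_w²)]. Assume between-subject SD 5 dB, within-person SD 2 dB, better-map mean 9 dB and worse-map mean 11 dB. The total SD is √(25 + 4) = 5.39.

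- Better map: (15 − 9)/5.39 = 1.11, so 13% excluded
- Worse map: (15 − 11)/5.39 = 0.74, so 23% excluded

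The rule hits both maps, but the worse one more often.

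**Effect on the estimate.** This was simulated with test and retest on each map, a constant true difference of 2 dB, between-subject SD 5 and test-retest SD 2. Any run above 15 dB is dropped, the surviving runs are averaged, and complete pairs are compared. Mean SRT is the midpoint of the two maps.

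| Mean SRT (dB) | Pairs lost | Estimate (true 2.00 dB) |
|---|---|---|
| 3 | 1% | 1.96 |
| 5 | 3% | 1.93 |
| 7 | 7% | 1.88 |
| 10 | 17% | 1.76 |
| 12 | 29% | 1.67 |

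The shrinkage is (2.00 − 1.96)/2.00 = 2% at the mild end and (2.00 − 1.67)/2.00 = about 17% at the severe end.

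**Sensitivity to unstated handling (mean SRT 10 dB).**

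- Limit applied to the test-retest mean: 1.89 dB.
- Both runs required to be valid: 1.87 dB, but 31% of pairs lost.

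**Sensitivity to the form of the effect.**

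- Person-to-person SD of 3 dB in the map difference, mean 10 dB: about 20% of pairs lost, estimate 1.68 dB.
- Map effect falling by 0.2 dB per dB of worse SRT, mean 10 dB: the estimate rises to 2.12 dB.
- No true difference: no bias, and type I error stays near 5%.

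**Power at N = 20, true difference 2 dB.** A paired rank test with scores above 15 dB kept at the limit was compared with exclusion:

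- Mean 10 dB with the 3 dB person-to-person SD: 57% against 41–45%.
- Mean 12 dB with a constant effect: 93% against 84–86%.

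Type I error is near 5% under either approach.

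**Capping is not enough if a mean is then taken.** Averaging values capped at 15 dB gives 1.64 dB at mean 10, below the 1.76 dB under exclusion. The gain comes from a rank or censored analysis.

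**The case against.** The strongest defence is that the limit is a validity rule with a cited source. Noise is fixed at 65 dB SPL, so an SRT above 15 dB puts speech above 65 + 15 = 80 dB SPL, where the adaptive result may be imprecise. That is a fair reason not to trust the exact value. It does not remove the information that the listener did worse than 15 dB, which is all a rank or a censored value uses.

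Several stronger readings are tempting, and the article does not support them:

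- **That the comparison is always biased towards no difference.** Shrinkage follows when the effect is constant or grows with severity. If the effect is smaller in poor performers, the paired estimate can rise.
- **That only the worse map loses its worst results.** The rule applies to both maps, and the better map loses scores too.
- **That the loss is material.** At low SRTs it is negligible, and the article does not show where this population lies.
- **That a failed run leaves the better run alone as the mean.** This is one possible reading; the article does not say how a single excluded run is handled.
- **That the in-noise learning curve loses its start.** Early failures are plausible, but learning curves are named only in general terms, with no in-noise curve specified.
- **That runs with too few reversals are floor results.** A 10-sentence run may simply not have converged, so this criterion is a separate validity check.

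The outcome is also secondary, and spatial hearing and listening effort bear on difficult listening too.

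**Conclusion.** The point holds as a design weakness in a secondary analysis. The article itself fixes an exclusion that depends on the result. When the maps differ, it usually falls more often on the worse map, removes pairs in which one map failed, lowers power and usually shrinks the estimate.

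The size cannot be derived from the article. Under the assumptions shown, a true 2 dB difference is estimated at about 1.96 dB (1% of pairs lost) to 1.67 dB (29% lost). It stays closer to 2 dB if the limit applies to the test-retest mean, and it can exceed 2 dB if poor performers show a smaller map effect. A reader might infer that a positive in-noise finding is invalid, but with no true difference the rule creates no bias. The primary CNC comparison is untouched.

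**What to change.** In the analysis plan, before database lock:

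1. Keep a score above 15 dB as worse than 15 dB. Compare the maps with a paired rank test (worst rank, tied when both maps exceed 15 dB) or a censored (Tobit) mixed model. Do not report a mean of values capped at 15 dB as the effect.
2. Apply this before test and retest are averaged, so that a failed run is not silently replaced by the better one.
3. Report the number of scores above 15 dB per map and visit.
4. Keep the fewer-than-two-reversals criterion as a separate validity check, and report its counts per map.

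The cost is a few lines of text. No new measurement is needed, because applying the present rule already requires knowing which scores pass 15 dB. The approach fits the nonparametric option that the article already allows. The downside is a result slightly harder to present than a mean in dB.
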